**Pregnancy outcomes**			
Preterm birth [23]	Preterm birth is defined by the WHO as babies born alive before 37 weeks of pregnancy are completed. It is further subcategorised based on gestational age: Extremely preterm (less than 28 weeks) Very preterm (28 to less than 32 weeks) Moderate to late preterm (32 to 37 weeks)	Pregnancies ending with live births	From time of vaccination to before week 37 of gestation (36 weeks and 6/7 days)
Time between vaccination and birth	Time between vaccination and birth in days.	Pregnancies ending with live and non-live births	From time of vaccination to time of birth
Stillbirth [24]	Stillbirth is defined by the WHO as the death of a foetus that has reached a birth weight of 500 g, or if birth weight is unavailable, gestational age of 22 weeks or crown-to-heel length of 25 cm. It is further subcategorised based on gestational age: Late foetal deaths (greater than 1000 g or after 28 weeks) Early foetal deaths (500–1000 g or 22–28 weeks)	Pregnancies ending with live and non-live births	From time of vaccination to end of pregnancy

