### 3.9. Study Size

All women meeting eligibility criteria during the study observation period should be included in the study. It is currently unknown how many women will receive RSV vaccination during pregnancy, as the National Immunisation Technical Advisory Groups need to determine whether this will be included in routine maternal immunisation programs in the country or region where the study is conducted. Minimal detectable risks can be calculated based on the assumption that every vaccinated pregnant individual could be compared with N unvaccinated pregnant individual(s) (1:N ratio). The desired alpha level is 5%, and risk ratio (RR) values of 1.5, 2.0, 2.5, and 4.0 may be considered (Supplementary Table S2). For pregnancy and birth outcomes, the required number of exposed women to achieve a power of 80% under different RR values may assume prevalence rates in the unexposed group ranging from 0.2% to 6.0%. To detect an RR of 1.5 with 95% confidence interval (CI) for preterm birth, approximately 1200 pregnancies ending in live birth would need to be included in a data source. For rare outcomes during pregnancy such as GBS, we calculated the power obtainable assuming a maximum sample size of 30,000 exposed pregnant women, with an incidence rate of 1/100,000 person-years in the comparator group [39].

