## 4. Discussion

This generic protocol has been developed to assess the safety of RSV vaccines in pregnant women and their offspring in real-world settings utilising secondary sources of data. It presents the emulation of a target trial, assessing the safety of administering a single dose of an RSV vaccine to pregnant women between 24–36 weeks of gestation compared to pregnant women who do not receive RSV vaccination during pregnancy [8]. The emulation of target trial conditions will help to reduce bias due to censoring, immortal time, competing events and confounding, improve the interpretability of estimands and highlight any remaining challenges with the data [17]. However, despite efforts to minimise bias and improve interpretability, limitations persist in target trial emulation using observational data. These may include challenges in accurately capturing all relevant confounders. Data sources that routinely collect data often provide comprehensive information on treatments and outcomes but may lack sufficient detail on clinical factors that require adjustment [47]. Fitness for purpose of data can be assessed in feasibility studies [18,19].

The study will use code lists or observations in birth registers to identify the covariates and outcomes of interest. An important consideration of using code lists is the potential for outcome misclassification, which can introduce bias and impact the interpretation of findings. The code lists could be sourced from Vaccine Monitoring Collaboration for Europe (VAC4EU) (https://vac4eu.org/), as these have undergone thorough review by medical professionals. Only codes labelled as “narrow” are included to mitigate the false-positive rate. For preterm birth, validation may be needed since preterm birth can either be spontaneous or medically indicated (iatrogenic), whereas our focus is only on spontaneous preterm birth. Codes and outcome definitions may be scrutinised in Safety Platform for Emergency Vaccines companion guides. Validation of outcomes, using Brighton or WHO definitions, may be conducted when resources are available.

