**Birth outcomes**			
Low birth weight (LBW) [28]	Low birth weight is defined by the WHO as a weight at birth of less than 2500 g, regardless of gestational age.	Pregnancies ending with live births	From birth until one month after birth
Small for gestational age (SGA) [29]	Small for gestational age is defined by the WHO as a birth weight below the 10th percentile for gestational age and sex. SGA can be caused by placental dysfunction, referred to as foetal growth restriction (FGR), or it can be due to a constitutionally small foetus without any pathological causes. Other possible causes include congenital malformations or infections.	Pregnancies ending with live births	From birth until one month after birth

**Table 3 vaccines-13-00272-t003:** Covariates of interest.

Covariate	Definition
Gestational age at time of vaccination	Gestational age at time of vaccination is defined as the time between the last menstrual period (LMP) and the date of vaccination, measured in weeks.
Calendar time at time of vaccination	Calendar time at the time of vaccination is defined as the specific calendar date of the vaccination, expressed in weeks (e.g., week 48 of the year 2024 or week 12 of the year 2025).
Maternal age	Maternal age at time of vaccination is defined as the age of the pregnant person at the date of vaccination. This age is determined by subtracting the individual’s date of birth from the date of vaccination.

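### Preterm birth, LBW and SGA are assessed in live births only, so a vaccine-related foetal death drops out of these estimates and can modestly dilute a harm; a composite beside each closes the gap

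*Protocol article*

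**What the plan says.** Table 2 has a column that fixes the pregnancies in which each outcome is ascertained.

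- **Preterm birth:** the definition reads "Preterm birth is defined by the WHO as babies born alive before 37 weeks of pregnancy are completed", and the column limits it to live births.
- **LBW and SGA:** the column reads "Pregnancies ending with live births".
- **Stillbirth, and time between vaccination and birth:** the column reads "Pregnancies ending with live and non-live births".

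The Discussion (Section 4) calls preterm birth the primary outcome measure. Section 3.9 gives its sample size in live births, about 1200 for an RR of 1.5. Section 3.10.2 recommends a separate analysis of time to birth to gain power for the preterm question. Section 3.1 places Time zero at vaccination, between 24 and 36 weeks.

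The Discussion also says that emulating a target trial "will help to reduce bias due to censoring, immortal time, competing events and confounding". This is the only mention of competing events. Nothing says how foetal death is handled for preterm birth, LBW or SGA, or that these outcomes are to be read together with stillbirth.

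**The concern.** A target trial fixes its analysis set at Time zero. Here the set for three key outcomes, including the primary one, depends on whether the foetus later survives to birth. Foetal death before 37 weeks competes with preterm live birth, may share causes with it, and could itself be affected by vaccination. If some pregnancies that would have ended in an early live birth end in foetal death instead, the vaccinated group loses preterm events and its preterm ratio falls. In a safety study that is the wrong direction.

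The companion analysis does not resolve this, because it uses a different population. A stillbirth at 30 weeks is an early end of pregnancy in the time-to-birth analysis and is absent from the preterm analysis. The two can diverge, and no rule says how to read them if they do.

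**Working it through.** **1. The plan's own figure.** Section 3.9 names a 5% alpha, 80% power, and "risk ratio (RR) values of 1.5, 2.0, 2.5, and 4.0 may be considered", with "prevalence rates in the unexposed group ranging from 0.2% to 6.0" per cent. I assume preterm birth sits at the top of that range, 6%, and test it against 9% (RR 1.5), two-sided, 1:1, pooled variance:

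n = [1.960·√(2·0.075·0.925) + 0.8416·√(0.06·0.94 + 0.09·0.91)]² / 0.03² = (0.7301 + 0.3130)² / 0.0009 ≈ 1209 exposed.

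This reproduces the stated 1200 as the exposed arm at 1:1 and supports 6% as the working value.

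**2. Model.** Let p = 0.06 be the preterm risk among live births, s the baseline risk of foetal death, r the vaccine's RR for foetal death, e = s(r − 1) the extra deaths, and f the share of those pregnancies that would otherwise have been preterm live births. All foetal deaths are taken to occur before 37 weeks, and the vaccine has no other effect.

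Live-birth RR = {[p(1 − s) − f·e] / (1 − s − e)} / p = 1 − e(f − p) / [p(1 − s − e)]

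The second form shows that the ratio is exactly 1 when f = p (deaths unrelated to preterm risk) and below 1 when f exceeds 6%. For s I use 0.2%, the lowest prevalence in Section 3.9. The section does not assign prevalences to outcomes, so p, s and f are assumptions.

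**3. Live-birth RR and the alternatives, s = 0.2%.** Worked case, doubling with f = 1: (0.05988 − 0.002)/0.996/0.06 = 0.969.

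| Foetal death | f | Live births only | Preterm live birth or foetal death, all pregnancies |
|---|---|---|---|
| Doubled | 1 | 0.969 | 1.000 |
| Doubled | 0.5 | 0.985 | 1.016 |
| Doubled | 0.06 | 1.000 | 1.030 |
| Fourfold | 1 | 0.905 | 1.000 |
| Fourfold | 0.5 | 0.956 | 1.048 |
| Fourfold | 0.06 | 1.000 | 1.091 |

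The composite is [p(1 − s) − f·e + s + e] / [p(1 − s) + s]. With s = 0.5% instead, the live-birth RR for f of 0.5 and 1 is 0.963 and 0.921 (doubling), or 0.888 and 0.760 (fourfold). The composite is again 1.000 or more.

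**4. Denominator change alone.** Counting preterm live births over all pregnancies with f = 1, as a cumulative incidence with foetal death as competing event would do, gives (0.05988 − 0.002)/0.05988 = 0.967 for a doubling and (0.05988 − 0.006)/0.05988 = 0.900 for a fourfold rise. These are slightly lower than 0.969 and 0.905. The missing events are in the numerator, so a new denominator does not restore them.

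**5. Dilution of a real harm.** Suppose the vaccine also multiplies preterm live births by 1.5 before these losses. With s = 0.2% the observed RR is [1.5·0.05988 − f·e]/(1 − s − e)/0.06. This is 1.486 (f = 0.5) or 1.470 (f = 1) for a doubling, and 1.459 or 1.408 for a fourfold rise.

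**6. Subcategories and other outcomes.** The bias scales with e/p. Table 2 splits preterm birth at 28 and 32 weeks. Where foetal death is common relative to live birth, as may be so at early gestations, the bias may be larger. The document gives no rates for these subcategories, nor separate rates for LBW and SGA, so I put no figure on them.

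**The case against.** **The bias is small and the death signal is sought elsewhere.** This largely stands. Stillbirth is a separate outcome in all births, and time to birth also retains foetal deaths. At 0.2% baseline, 1:1 and 80% power, stillbirth needs 11,737 exposed women for RR 2 and about 2,170 for RR 4. A programme that reaches tens of thousands would see the scenarios in which the bias is material. At the 1200 given for preterm birth, power for a stillbirth RR of 2 is only 14%. However, the 95% interval around a preterm RR of 1 is then roughly 0.73 to 1.37, since 1.96·√(2·0.94/72) = 0.317, and a 3% bias is lost in it. None of this corrects the preterm, LBW and SGA estimates themselves.

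**Stillbirth is too rare to act as a safeguard.** A reader might infer this stronger point from the roughly 39,100 exposed needed for RR 1.5 at 0.2%, against the 30,000 in Section 3.9. The document does not support it. That requirement holds only at 1:1, and the plan matches 1:N: it is about 28,600 at 1:2 and 23,200 at 1:4. Section 3.9 also gives 30,000 for rare outcomes such as GBS, not as a limit for stillbirth. At RR 1.5 the worst-case preterm bias is in any case only 0.984.

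**Born-alive is the WHO definition, and detail belongs in the SAP.** The definition is not at fault and should stay, since Section 3.7 recommends official definitions for comparability. Section 3.10 does defer detailed methods. But Table 2 states the analysis population outright, so the restriction is a fixed rule and not an omitted detail.

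**Conclusion.** The point holds as a modest, cheap improvement. Three estimates, including the primary one, are conditioned on survival to live birth after Time zero, and the Discussion's claim about competing events has no method behind it for these outcomes. At 6% preterm birth and 0.2% foetal death, the preterm RR is pulled to between 0.969 and 1.00 by a doubling of foetal death, and to between 0.905 and 1.00 by a fourfold rise. The lower ends require every extra death to come from a pregnancy that would have been a preterm live birth.

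A reader might infer that a harmful vaccine would look clearly protective. For overall preterm birth these figures do not show that; attenuation of a real harm is the more likely consequence. The size rests on the assumed p, s and f, and for the early-gestation subcategories it cannot be judged from the document.

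**What to change.** Keep the WHO live-birth outcome. Beside it, prespecify a composite over all pregnancies matched at Time zero: live preterm birth or foetal death before 37 weeks. Do likewise for LBW and for SGA (affected live birth or foetal death). State that each pair is read jointly with stillbirth. Report time to birth for live births only as well as for all births, so that one version shares the preterm population. Do not rely on a changed denominator or cumulative incidence alone.

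One condition needs checking. Section 3.5 excludes women who cannot be linked to their child. Where a foetal death leaves no child record, that rule could remove the very events that the composite and the stillbirth outcome need.

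The cost is a few sentences and one extra row per outcome, since stillbirth is already an outcome of the study. The downside is one more estimate per outcome to explain, and a composite that mixes events of different severity.

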**Maternal outcomes**			
Hypertensives disorders of pregnancy [25,26]	Hypertensives disorders of pregnancy include: Gestational hypertension (defined as systolic blood pressure greater than or equal to 140 mm/Hg and/or diastolic blood pressure greater than or equal to 90 mm/Hg arising de novo at ≥20 weeks’ gestation in the absence of proteinuria or other findings suggestive of pre-eclampsia) Preeclampsia de novo (defined as gestational hypertension accompanied by one or more of the following new-onset conditions at ≥20 weeks’ gestation: (a) Proteinuria (b) Other maternal end-organ dysfunction, including neurological complications, pulmonary oedema, haematological complications, renal insufficiency, or impaired liver function (c) Uteroplacental dysfunction Preeclampsia superimposed on chronic hypertension (among persons with chronic hypertension, development of new proteinuria, another maternal organ dysfunction(s), or evidence of uteroplacental dysfunction HELLP (Haemolysis, Elevated Liver Enzyme, Low Platelet) is a serious manifestation of pre-eclampsia and should be assessed if available.	Pregnancies ending with live and non-live births	From time of vaccination to end of pregnancy
Guillain-Barré Syndrome (GBS) [27]	GBS is defined as an neurological condition in which a person’s immune system attacks the peripheral nerves. It is a rare condition and the cause of it is not fully understood. Most cases follow an infection with a virus or bacteria, e.g., Campylobacter jejuni, cytomegalovirus, Epstein-Barr virus and the Zika virus. In rare instances, vaccinations may increase the risk of people getting GBS.	Pregnancies ending with live and non-live births	From time of vaccination until 42 days following vaccination
**Birth outcomes**			
Low birth weight (LBW) [28]	Low birth weight is defined by the WHO as a weight at birth of less than 2500 g, regardless of gestational age.	Pregnancies ending with live births	From birth until one month after birth
Small for gestational age (SGA) [29]	Small for gestational age is defined by the WHO as a birth weight below the 10th percentile for gestational age and sex. SGA can be caused by placental dysfunction, referred to as foetal growth restriction (FGR), or it can be due to a constitutionally small foetus without any pathological causes. Other possible causes include congenital malformations or infections.	Pregnancies ending with live births	From birth until one month after birth

**Table 3 vaccines-13-00272-t003:** Covariates of interest.

Covariate	Definition
Gestational age at time of vaccination	Gestational age at time of vaccination is defined as the time between the last menstrual period (LMP) and the date of vaccination, measured in weeks.
Calendar time at time of vaccination	Calendar time at the time of vaccination is defined as the specific calendar date of the vaccination, expressed in weeks (e.g., week 48 of the year 2024 or week 12 of the year 2025).
Maternal age	Maternal age at time of vaccination is defined as the age of the pregnant person at the date of vaccination. This age is determined by subtracting the individual’s date of birth from the date of vaccination.
Immunocompromised status	Immunocompromised status is defined as meeting at least one of the following criteria at the time of vaccination or in the period prior to vaccination: Medical conditions (a) Diagnosed with symptomatic HIV/AIDS (b) Diagnosed with hematologic malignancy (e.g., chronic lymphocytic leukaemia, non-Hodgkin lymphoma, multiple myeloma, acute leukaemia) (c) Diagnosed with solid malignancy (d) Diagnosed with rheumatologic/inflammatory conditions (e.g., Sjogren’s syndrome, SLE, psoriatic arthritis, rheumatic arthritis, arthritis spondylarthritis, polymyalgia rheumatica, demyelination multiple sclerosis, polymyalgia rheumatica, IBD, autoimmune thyroiditis) and have evidence of treatment with chemotherapy or immune modulators (see below) Immunosuppressive treatments (a) Organ transplant recipients or islet transplant recipients taking immunosuppressive therapy (b) CAR-T-cell therapy or hematopoietic stem cell transplant recipients taking immunosuppressive therapy (c) Rheumatologic/inflammatory conditions treated with systemic corticosteroids (d) Active treatment (at time of vaccination) with various immunosuppressive agents (e.g., systemic corticosteroids, alkylating agents, antimetabolites, transplant-related immunosuppressive drugs, cancer chemotherapeutic agents classified as severely immunosuppressive, TNF blockers, and other biologic agents that are immunosuppressive or immunomodulatory). Specific medical procedures (a) Organ transplant recipients or islet transplant recipients (b) CAR-T-cell therapy or hematopoietic stem cell transplant recipients
High-risk pregnancy	High-risk pregnancy is defined as pregnancies in which women or their offspring have a history of any of the following conditions in the current pregnancy (prior to vaccination): Obesity Hypertension Pre-eclampsia/eclampsia Multifetal pregnancy Diabetes Gestational diabetes Congenital anomaly And/or any of the following conditions in previous pregnancies: Gestational diabetes Pre-eclampsia/eclampsia Stillbirth or late miscarriage Small for gestational age or foetal growth restriction Congenital anomaly

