## 3. Methods

### 3.1. Study Design

We recommend an observational retrospective comparative cohort study of pregnant women who receive the RSV vaccine compared to an unexposed pregnant comparator group (or an active comparator group when there is one). To assess whether the RSV vaccine increases the risk of any adverse outcome in pregnancy or offspring, we propose designing the study to emulate a hypothetical pragmatic randomised trial (Table 1) [16]. This trial would assess the safety of administering one dose of the RSV vaccine between 24 and 36 weeks of gestation in pregnant women compared to pregnant women who do not receive an RSV vaccine (Figure 1A). As we cannot truly randomise participants, we need to emulate this feature by carefully addressing confounding biases through various techniques such as matching and careful assessment of inclusion criteria. These techniques also have the potential to address both selection bias and immortal time bias. Time zero, designated as day 0, marks the point at which the eligibility criteria are fulfilled, and the RSV vaccine is administered to the pregnant woman.

At Time zero, exposed participants should be matched to unexposed pregnant participants eligible to receive the vaccine (1:N ratio) based on (Figure 1B):Gestational age (same week of gestation) to account for timing of vaccination in pregnancy and the risk of preterm birthCalendar time (same week) because of RSV seasonality and probability of exposureMaternal age (year of birth) because of the association with adverse pregnancy outcomesImmunocompromised status because of the association with adverse maternal outcomesHigh-risk pregnancy because of the association with adverse pregnancy outcomes

Additional characteristics may be added that would confound the association.

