### 3.5. Recommended In- and Exclusion Criteria

Participants are eligible if they:have an identified start of pregnancy date.are enrolled in the healthcare system for a least 12 months prior to Time zero (date of vaccination).have at least one day of follow-up after Time zero for maternal outcomes and at least 10 months of follow-up after the LMP for birth and pregnancy outcomes.

Participants are excluded if they:are exposed to an RSV vaccine prior to the current pregnancy or before or after the gestational week for which the vaccine is licensed (vaccination in a prior pregnancy is permitted).cannot be linked in the data source to their child (mother-child linkage).

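### Women already expected to deliver preterm are not screened out at Time zero, and Table 3's open-ended corticosteroid item can place some of them among the immunocompromised comparators

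*Protocol article*

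**What the plan says.** **Corticosteroid item.** Table 3 requires only one criterion for immunocompromised status. Item (d) under immunosuppressive treatments is "Active treatment (at time of vaccination) with various immunosuppressive agents (e.g., systemic corticosteroids", followed by other drug classes. It gives no indication, dose or duration. Item (c) of the same list already covers systemic corticosteroids for rheumatologic or inflammatory conditions, so (d) adds use for other reasons. The flag is a matching variable (Section 3.1, Table 1) and defines a subgroup in the secondary objectives (Sections 2 and 3.10.2).

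**Eligibility.** Section 3.1 says: "At Time zero, exposed participants should be matched to unexposed pregnant participants eligible to receive the vaccine". Eligible to receive is not defined further there. Section 3.5 asks for a pregnancy start date, 12 months of enrolment and follow-up; for maternal outcomes women must "have at least one day of follow-up after Time zero for maternal outcomes". Its only exclusions are RSV vaccine exposure outside the permitted timing and missing mother-child linkage. Table 1 drops the target trial's restriction to uncomplicated pregnancies and relies on stratification by high-risk pregnancy. The high-risk list in Table 3 contains no labour, ruptured membranes or threatened preterm labour.

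**Outcome window.** Table 2 sets the preterm window as "From time of vaccination to before week 37 of gestation (36 weeks and 6/7 days"), so it opens at once. Section 3.1 recommends separate trials for each gestational week from 24 to 36 to study effect modification.

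**The concern.** Preterm birth is named in the Discussion as the primary outcome measure. A woman admitted in threatened labour is formally within the licensed weeks and can be drawn as a comparator, yet she is unlikely to be vaccinated that week. If so, comparators include women whose preterm birth is already under way and the vaccinated arm has few of them. The RR then moves down, so that a null effect looks protective or a harm looks smaller.

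There are two distinct routes:

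1. The corticosteroid item affects the immunocompromised subgroup, which is of interest because the pre-licensure trial excluded such women.
2. The eligibility gap affects the overall comparison. It matters most in late gestational weeks, where the window is short and a false gradient by week could be read as effect modification.

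**Working it through.** **The plan's own figure.** Section 3.9 states "The desired alpha level is 5"%, "the required number of exposed women to achieve a power of 80"%, and "prevalence rates in the unexposed group ranging from 0.2% to 6.0"%. It then says: "To detect an RR of 1.5 with 95% confidence interval (CI) for preterm birth, approximately 1200 pregnancies ending in live birth would need". With 6% versus 9% (6% is the top of the stated range, assumed here for preterm birth), two-sided alpha and 1:1 allocation, the usual two-proportion formula gives 1,209 exposed women. The figure therefore reproduces as exposed women at 1:1 and is not disputed. Power at 1,200 per arm is 0.80.

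The article gives no frequency for any of the states below. Every input from here on is an assumption, and the true RR is 1 unless stated.

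**1. Immunocompromised subgroup.** Let t be the share truly immunocompromised, and a the share of eligible comparators flagged only through an antenatal steroid course. No vaccinated woman is in the second state, and the courses are recorded in the data source. Preterm risk is 10% in the truly immunocompromised and 40% in the misfiled.

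- Misfiled share f = a/(t + a); comparator risk = (1 − f) × 10% + f × 40%; RR = 10% / comparator risk.
- t = 2%, a = 0.3%: f = 0.3/2.3 = 13%; risk 13.9%; RR 0.72.
- t = 1%, a = 0.5%: f = 33%; risk 20.0%; RR 0.50.
- t = 3%, a = 0.1%: f = 3.2%; risk 11.0%; RR 0.91.

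**2. Whole pool, mixing calculation.** A fraction f of comparators is about to deliver, with preterm risk r; base risk is 6%. Comparator risk = (1 − f) × 6% + f × r.

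- f = 0.3%, r = 40%: 6.10%; RR 6/6.10 = 0.98.
- f = 1%, r = 50%: 6.44%; RR 0.93. A true RR of 1.5 reads 9/6.44 = 1.40, and power at 1,200 per arm falls from 0.80 to 0.65.
- Over f from 0.1% to 2% and r from 30% to 70%: RR 0.996 to 0.82.

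**3. Does the corticosteroid flag drive the overall result?** Take f = 1%, r = 50%, with all such women flagged and 1% to 3% of vaccinees truly immunocompromised. Flagged comparators can now be matched only to flagged vaccinees. At 2%, the flagged comparators' risk is (2/3) × 6% + (1/3) × 50% = 20.7%, and the overall matched comparator risk is 98% × 6% + 2% × 20.7% = 6.29%, RR 0.95. Across 1% to 3% the RR is 0.965 to 0.948, against 0.932 without the flag. Matching on the flag reduces the overall bias and concentrates it in the subgroup.

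**4. By gestational week.** Extreme rule: no woman who will deliver within 2 days is vaccinated. Time zero is mid-week (day 3). Daily birth hazards are flat, or double every 30, 20, 14, 10 or 7 days. Births on days 1 and 2 are removed from the vaccinated arm only. With flat hazards the RR is simply the remaining days over the window: week 36, 1/3; week 35, 8/10; week 34, 15/17; week 32, 29/31.

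| Week of vaccination | RR across hazard shapes |
|---|---|
| 32 | 0.94 to 0.99 |
| 34 | 0.88 to 0.95 |
| 35 | 0.80 to 0.87 |
| 36 | 0.33 to 0.37 |
| Pooled 24–36, vaccination days evenly spread | 0.96 to 0.97 |
| Pooled 32–36, vaccination days evenly spread | 0.89 to 0.92 |

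**The case against.** The strongest reply is that this is a generic framework with several hooks. Comparators must be eligible for vaccination, extra matching characteristics and covariates are invited (Supplementary Table S1 is not shown), propensity scores may be used, and separating steroid indications is partly code-list work. These hooks could help, but none is fixed for this problem. The optional analysis excluding iatrogenic births leaves women in spontaneous threatened labour untouched.

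It is also fair that the direction is inferred: equal frequency of these states in both arms would remove the shift. The subgroup bias arises only where in-hospital courses are recorded, and the subgroup analysis itself is optional.

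A reader might infer four stronger things that the document does not support:

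- **That the corticosteroid item biases the overall preterm result.** Step 3 shows the opposite.
- **That any course before vaccination counts.** The table's lead-in mentions the prior period, but item (d) itself limits the criterion to treatment active at vaccination.
- **That an RR near 0.33 is typical.** It comes from deleting two days of a three-day window under an all-or-nothing rule; the pooled figure under the same rule is 0.96 to 0.97.
- **That nearly all preterm births in the week-35 trial are already imminent at Time zero.** Under the two-day rule the share at week 35 is 13% to 20%.

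**Conclusion.** The point holds as two separate, moderate defects.

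1. Item (d), read literally, admits short antenatal corticosteroid courses into the immunocompromised definition. If those women are rarely vaccinated and their courses are recorded, the subgroup's preterm RR is biased towards safe: 0.72 under a true null in the illustration, range 0.50 to 0.91.
2. Eligibility and the high-risk list leave women about to deliver in the comparator pool, with no lag in the window. If they are vaccinated less often, the pooled bias is a few percent under most of the assumed inputs (RR about 0.93 to 0.98, down to 0.82 at the extreme). It is larger in weeks 34 to 36, where it could pass for effect modification by week.

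The gaps are in the text. The direction rests on lower vaccination among these women, and all the sizes rest on assumed frequencies and risks.

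**What to change.** **Table 3, item (d).** Restrict the corticosteroid criterion to an immunological indication, or to repeated or prolonged treatment, so that antenatal courses for fetal lung maturation do not set the flag.

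**Section 3.5.** At Time zero, and in both arms, exclude women with a code for labour, ruptured membranes or threatened preterm labour, or else match on these codes.

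**Section 3.10.2.** Add a sensitivity analysis omitting births in the first days after Time zero, to reach women who go into labour soon after with no code on the day. State the weeks to which it applies: the preterm window is at most 6 days for week 36 and 13 for week 35, so a 7-day lag leaves nothing in week 36 and removes more than half of week 35.

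**Cost.** This is wording and code lists, mostly on data already extracted, with slightly fewer comparators. Codes for threatened labour will be incomplete in some sources, so some bias will remain and should be reported as a limitation.
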